#### Missing data

The numbers of patients with missing data for one or more CMR measurements, and the number of uninterpretable images will be reported. Patients with missing data for any CMR measurement will be excluded from any comparison involving that measurement.

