## Methods/Design

### Study design

CADERA bolts on to the VEDERA (Very Early versus Delayed Etanercept in Rheumatoid Arthritis) trial, a prospective longitudinal intervention study of patients with early RA, randomized to either first-line TNFi therapy (etanercept, ETN) and MTX or optimal synthetic DMARD therapy. VEDERA is an investigator-initiated research (IIR) study based at the Leeds Institute of Rheumatic and Musculoskeletal Medicine, and is funded by an unrestricted educational grant that is part of an IIR agreement with Pfizer. VEDERA is a phase IV, single-centre study of 120 patients with new-onset, treatment-naïve RA, randomized to either immediate ETN and MTX combination or initial MTX and a treat-to-target regimen (optimal, standard conventional therapy approach); with step-up in the latter group to ETN and MTX combination therapy in patients failing to achieve a pre-defined target of remission after 24 weeks. The aim of VEDERA is to assess for the depth of remission (clinical and imaging) and immunological normalization induced by the treatment arms, as well as to identify predictors of remission.VEDERA patients will be recruited to CADERA and undergo CMR at baseline (prior to treatment) as well as after one and two years of treatment (see Figure 1). The change in CVD status as defined by CMR between baseline and follow-up in patients treated with early biological or optimal DMARD therapy will be determined. The study flow chart is presented in Figure 1. At the end of the study all patients will enter an inflammatory arthritis registry based at the National Institute for Health Research (NIHR) Leeds Musculoskeletal Biomedical Research Unit (LMBRU).

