### Primary outcome measure

The primary outcome measure is aortic distensibility. It will be measured and quantified at baseline and at one year in each arm of the study. Increased arterial stiffness is associated with an increased risk of CV events [9]. It can be measured by pulse wave velocity or as distensibility of the aorta, but requires careful correction for age and blood pressure. It has previously been shown that aortic distensibility relates to clinical outcome and that TNFi improve aortic distensibility [27]. We performed a pilot study in 10 patients with RA (disease duration 20 ± 9.6 years) and matched by age and gender to 10 asymptomatic subjects without RA. Aortic distensibility was significantly different in RA patients, with a mean and standard deviation of 1.83 ± 0.4 cm^2^ versus 2.6 ± 0.6 cm^2^ in controls. LV volumes and mass were similar between groups and LV strain and twist showed trends towards a reduction in RA patients, but without reaching statistical significance. Our pilot data therefore suggested CV abnormalities in patients with RA in several quantitative CMR parameters, with aortic distensibility reaching statistically significant difference even in the small sample size.

Longitudinal changes of outcome measures in response to therapy will be measured and compared between the two treatment arms at baseline, one and two year time points. Secondary outcome measures are i) myocardial perfusion reserve, ii) LV strain and twist, iii) LVEF and iv) LV mass. Exploratory outcome measures are pre- and post-contrast T1 mapping, extra-cellular volume (ECV) and biomarker measurements.

Significant differences (expressed as *P* <0.05) of CV abnormalities detected by CMR between the two treatment arms will be presented, and the magnitude of this difference will be expressed as a 95% confidence interval.

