### Sample size calculation

Power calculations are based on a previous study by Ikonomidis *et al*. [28]. We assumed an effect size of 2.46 cm^2^dyne^-1^10^-6^, representing 75% of the difference between treated (Anakinra) and non-treated RA patients reported by Ikonomidis *et al*. [28]. Mean aortic distensibility at baseline to post-treatment for treated and non-treated patients was 1.56 cm^2^dyne^-1^10^-6^ and 4.6 cm^2^dyne^-1^10^-6^, respectively. The standard deviation (SD) of the post-treatment measurements in the Anakinra group was 3.2 cm^2^dyne^-1^10^-6^ and a more conservative estimate of 3.5 cm^2^dyne^-1^10^-6^ has been used in the CADERA power calculation. Assuming an SD of 3.5 cm^2^dyne^-1^10^-6^, a power of 70%, 80% and 90% would be achieved at 5% significance level in a two-tailed independent samples Student’s t-test with 26, 33 and 44 patients respectively in the primary outcome measure of aortic distensibility in each treatment group (30, 38 and 50 when adjusted for 10% dropout).

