Both treatment arms will be compared with primary outcome aortic distensibility from baseline to one-year follow-up, as well as other outcome measures. Analysis will be conducted in the R environment for statistical computing (R Core Team, 2012. R: A language and environment for statistical computing. R Foundation for Statistical Computing, Vienna, Austria). Exploratory data analysis will be used to determine if parametric (independent samples Student’s t-test) or non-parametric (Wilcoxon rank sum test) analyses are appropriate, and to summarize the distribution of aortic distensibility and change in other outcome measures across the two treatment arms. These analyses will also allow the credibility of an equal variance assumption to be assessed in parametric modeling and to be appropriately modeled [42]. All patients meeting eligibility criteria will be included in the analyses and these will be conducted at the end of the recruitment period. Exploratory subgroup analyses will be conducted separately by other comorbidities, a maximum of two to three that are clinically plausible, with appropriate correction for multiple testing [43]. Interactions between subgroups and interactions between CMR findings and biomarkers will be explored through building a linear model with interaction terms [44]. Patterns of CVD pathology in RA patients will be described. Treatment effects on secondary outcome measures and effects at the two-year follow-up point will be analyzed in an equivalent manner.

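### The one-year arm comparison is an unadjusted test on patients with complete scans; it is biased if drop-out depends on baseline distensibility and differs between arms, and adjusting for baseline removes that bias

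*Protocol article*

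**What the plan says.** All references are to the protocol article.

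- **Missing data.** The rule is stated outright: "Patients with missing data for any CMR measurement will be excluded from any comparison involving that measurement". The section also promises counts of missing and uninterpretable measurements, but does not say that these will be given by arm.
- **Sample size calculation, analysis paragraph.** The primary contrast is described as "Both treatment arms will be compared with primary outcome aortic distensibility from baseline to one-year follow-up, as well as other outcome measures". Exploratory analysis is to "determine if parametric (independent samples Student’s t-test) or non-parametric (Wilcoxon rank sum test) analyses are appropriate". Neither test takes a covariate. Later time points follow the same route: "Treatment effects on secondary outcome measures and effects at the two-year follow-up point will be analyzed in an equivalent manner". The same paragraph says "All patients meeting eligibility criteria will be included in the analyses".
- **Sample size calculation, first paragraph.** Drop-out enters only as an inflation of the number per arm: "30, 38 and 50 when adjusted for 10% dropout".
- **Study design.** Patients are to "undergo CMR at baseline (prior to treatment) as well as after one and two years of treatment", so a pre-treatment value is scheduled for everyone.
- **Primary outcome measure.** The article says that arterial stiffness "requires careful correction for age and blood pressure", yet the stated arm comparison adjusts for nothing.

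**The concern.** The exclusion rule and the unadjusted test have to be read together. A patient who misses the one-year scan leaves the one-year contrast, and the test has no means of correcting for any difference in starting level between the patients who remain in each arm. Randomisation balances baseline distensibility among all patients randomised, but not necessarily among those who return with a usable scan.

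Differential loss is conceivable here. The scan takes about an hour, and the aortic cine comes after adenosine stress in the listed sequence. Some of the listed contraindications (asthma, high-grade heart block, renal failure) could arise during follow-up. The two arms also follow different regimens. None of this shows that loss will depend on arm and baseline; it means only that the analysis should not rely on its absence.

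At stake is the primary estimate. The direction of bias also depends on whether change or the one-year value is tested, and the wording does not settle which.

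**Working it through.** **1. The plan's own figure.** Inputs from Sample size calculation: difference 2.46, SD 3.5, two-sided 5%. Exact non-central t power is 70.0%, 80.3% and 90.3% at 26, 33 and 44 per arm, so the stated numbers reproduce. Dividing by 0.90 gives 28.9, 36.7 and 48.9, that is 29, 37 and 49 against the stated 30, 38 and 50, a harmless extra patient in each case. Drop-out is therefore budgeted for power. What remains is bias.

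**2. Set-up for bias.** From the article: SD 3.5, design effect 2.46, planned drop-out 10%. Assumed, because the article gives no figures:
- SD 3.5 at both visits, with a linear relation between them and correlation ρ of 0.3, 0.5 or 0.7;
- in the etanercept-first arm, 10% missing, unrelated to baseline;
- in the control arm, 10% or 20% missing, with logit P(missing) = a − z, where z is baseline distensibility in SD units. The odds of a missing scan rise 2.7-fold per SD lower baseline.

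**3. Formula.** Let S be the mean baseline of retained controls minus the mean baseline of retained etanercept-first patients. For the etanercept-first minus control difference:
- bias of the change comparison = +(1 − ρ) × S
- bias of the one-year-value comparison = −ρ × S

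**4. Numbers.** For 10% missing, a = −2.564 and the retained controls have mean z = 0.0908, so S = 0.0908 × 3.5 = 0.318. For 20% missing, a = −1.650 and mean z = 0.1732, so S = 0.1732 × 3.5 = 0.606.

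| Missing (etanercept-first v control) | ρ | Bias, change | Bias, one-year value |
|---|---|---|---|
| 10% v 10% | 0.3 | +0.22 (9.0%) | −0.10 (3.9%) |
| 10% v 10% | 0.5 | +0.16 (6.5%) | −0.16 (6.5%) |
| 10% v 10% | 0.7 | +0.10 (3.9%) | −0.22 (9.0%) |
| 10% v 20% | 0.3 | +0.42 (17.3%) | −0.18 (7.4%) |
| 10% v 20% | 0.5 | +0.30 (12.3%) | −0.30 (12.3%) |
| 10% v 20% | 0.7 | +0.18 (7.4%) | −0.42 (17.3%) |

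Percentages are of 2.46, in absolute value.

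**5. When the bias vanishes.** With drop-out unrelated to baseline, S = 0 even at 10% v 20%. With the same rate and the same dependence in both arms, the two shifts cancel and S = 0. With the same dependence but 10% v 20%, S = 0.606 − 0.318 = 0.288, and the bias is 0.09 to 0.20.

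**6. Baseline adjustment.** ANCOVA of the one-year value on arm and baseline, fitted only to patients with both scans, gave a bias of at most 0.01 in large simulations of every scenario in the table. Exclusion was still in force in that check.

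**7. Scale.** If all 120 VEDERA patients join, 60 per arm less 10% leaves 54. The standard error of an unadjusted difference is then 3.5 × √(2/54) = 0.67. Every bias in the table is smaller than one standard error.

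**The case against.** The strongest reply is that the exclusion rule is not itself the culprit. Complete-case ANCOVA is practically unbiased in these scenarios, so what matters is the absent baseline covariate. That stands, and the fix is framed accordingly. A repeated-measures model would also use partial data, but its gain was not calculated here.

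Four stronger readings are tempting and are not supported.

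- A reader might infer that baseline and two-year scans are thrown away. Exclusion applies per comparison: the baseline scan still serves the baseline description, and the two-year scan the two-year comparison. They are lost only to the one-year contrast.
- A reader might infer that the sentence including all eligible patients contradicts the Missing data section. The first says who enters the analyses and the second what happens when a measurement is absent. A linking clause is all that is needed.
- A reader might infer that the comparison is valid only if missingness is unrelated to arm and to baseline. Step 5 shows otherwise: bias requires dependence on baseline together with a difference between arms in rate or strength.
- A reader might infer that such drop-out is to be expected. The article has no data on who drops out.

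It is also fair to credit the article with reporting missing and uninterpretable scans and, under Test conduct, the reasons for incomplete scans. Further sensitivity analyses may sit in a fuller document that is not shown, so their absence is not counted here.

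**Conclusion.** The point holds in a limited, conditional form. The article fixes an unadjusted two-sample test on patients with complete scans, which leaves the primary estimate open to bias if drop-out depends on baseline distensibility and differs in rate or strength between arms. With dependence in one arm only and ρ between 0.3 and 0.7, the absolute bias is about 0.1 to 0.2 units (4% to 9% of 2.46) at the planned 10% per arm, and about 0.2 to 0.4 units (7% to 17%) at 10% v 20%. These sizes rest on the assumed correlation, drop-out slope and equal SDs, none of which the article gives. The bias is modest beside the standard error, but more patients would not shrink it and it is cheap to prevent. The change should be made, though this is not a fatal defect.

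**What to change.** 1. Make the primary one-year arm comparison baseline-adjusted. Either use ANCOVA of one-year distensibility with baseline distensibility as covariate, or a repeated-measures model of the scheduled scans with a common baseline mean that includes every randomised CADERA patient with a usable aortic measurement. Name one in advance.
2. Keep the unadjusted complete-case test as a sensitivity analysis.
3. Report missing and uninterpretable scans by arm.
4. Add a clause to the analysis paragraph stating that its sentence on including all eligible patients is subject to the Missing data section.

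The cost is a little more analysis work in R, which the article already names; no extra scans, visits or patients are needed. Either model relies on scans being missing at random given the observed scans, and neither protects against drop-out that depends on the unseen one-year value.

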#### Test conduct

The number of patients referred from VEDERA and failing to complete the CMR protocol will be reported, along with the reason why the test failed. The duration of the CMR scan will also be summarized.

### Cardiac magnetic resonance investigation details

Our group has well-established multi-parametric protocols that have been validated in other populations [45]. CMR will be performed on a dedicated 3 T Philips Achieva TX system equipped with a 32-channel coil, vectorcardiographic triggering and multi-transmit technology (Philips Healthcare, Best, The Netherlands). Patients will be asked to avoid caffeine for 24 hours prior to the scan. The CMR protocol (Figure 2) lasts approximately 60 minutes and will comprise of:

**Figure 2 Fig2:**
[figure not shown]
**Coronary Artery Disease Evaluation in Rheumatoid Arthritis (CADERA) cardiac magnetic resonance protocol.** LGE, late gadolinium enhancement; LV, left ventricular; MOLLI, modified Look-Locker inversion method; SPAMM, spatial modulation of magnetization.

Low-resolution survey, reference scans and localizers. Following survey and reference scans, the heart’s short axis, vertical long axis and horizontal long axis will be defined with a series of cine images (balanced steady-state free precession acquisition (bSSFP), echo time (TE) 1.48 ms, repetition time (TR) 3.0 ms, flip angle 45°, field of view 320 to 420 mm according to patient size, slice thickness 10 mm and 30 phases per cardiac cycle).Baseline T1 mapping. One slice will be acquired at the LV short axis using an electrocardiogram (ECG)-triggered modified Look-Locker inversion (MOLLI) method to acquire 11 images (3-3-5 acquisition with 3 × R-R interval recovery epochs) in a single end-expiratory breath hold (voxel size 1.7 × 2.14 × 10 mm^3^ trigger delay at end-diastole, flip angle 35° and field of view 320 to 420 mm) [46, 47].Adenosine stress first-pass myocardial perfusion imaging (spoiled Turbo Gradient Echo, 5 × k-t Broad-use Linear Acquisition Speed-up Technique, 11 training profiles, 1.31 × 1.32 × 10 mm^3^ acquired resolution, pre-pulse delay 100 ms, acquisition shot 123 ms/slice, three short axis slices) [48]. Intravenous adenosine will be administered at 140 mcg/kg/min for three minutes under continuous ECG monitoring. Adequate hemodynamic response is assessed by either i) heart rate increase by ≥10%, ii) systolic blood pressure decrease of ≥10 mmHg or iii) symptoms attributed to adenosine administration. If there is inadequate hemodynamic response then the dose will be increased to 170 and then to 210 μg/kg/min for a further two minutes until hemodynamic response is achieved. The contrast injection will be performed using a dual-bolus technique, by intravenous route in the ante-cubital fossa, of 0.1 mmol/kg of gadolinium-DTPA (diethylene triamine pentaacetic acid) (gadopentetate dimeglumine; Magnevist, Bayer, Berlin, Germany) for the main bolus, preceded by the same volume of a 10% dilute contrast agent dose for the pre-bolus, both administered at a rate of 4.0 ml/s, followed by a saline flush using a using a power injector (Spectris, Solaris, Pennsylvania, United States) [49].Resting wall motion and LV function. Cine image stack covering the entire heart in the LV short axis plane at one slice per breath-hold in end-expiration and parallel to the mitral valve annulus (bSSFP, multiphase, 10 to 12 contiguous slices, spatial resolution 2.0 × 1.63 × 8 mm^3^ and 30 cardiac phases) [50, 51].Tissue tagging for strain analysis and diastology. Spatial modulation of magnetization pulse sequence (spatial resolution 1.51 × 1.57 × 10 mm^3^, tag separation 7 mm, ≥18 phases, typical TR/TE 5.8/3.5 ms and flip angle 10°).Aortic distensibility. Cine images of the ascending aorta (50 phases) at the level of the PA bifurcation and the descending aorta, transverse to the vessel according to Lee *et al*. [35]. For aortic stiffness, blood pressure and heart rate are recorded immediately prior to the multi-phase SSFP cine image (24 phases).Resting first-pass myocardial perfusion study. Pulse sequence, slice positioning and injection characteristics identical to the stress perfusion scan as above in step 3.Late gadolinium enhancement (LGE). Performed between 10 and 15 minutes after step 7. Inversion recovery-prepared T1-weighted gradient echo. The optimal inversion time to null signal from normal myocardium will be determined using a modified Look-Locker approach [52]. Typical parameters: TE 2.0 ms, TR 3.5 ms, flip angle 25°, acquired spatial resolution 1.54 × 1.76 × 10 mm^3^. Inversion time adjusted according to variable TI scout. Alternate heart beat acquisitions by navigator is an option for poor breath holders. Performed in 10 to 12 short axis slices with further slices acquired in the vertical and horizontal long axis orientations, or phase-swapped, if indicate based on LGE imaging obtained, wall-motion or perfusion defects.Post-contrast T1 mapping 15 minutes following last contrast injection at step 7. Acquisition and slice positioning as above in step 2.

T1 mapping, tissue tagging and perfusion imaging are performed in three identical short-axis positions. These will be determined using the ‘three-of-five’ approach by acquiring the central three slices of five parallel short-axis slices spaced equally from mitral valve annulus to LV apical cap [53].

### CMR image analysis and reporting

Image analysis will be performed offline, blinded to patient characteristics and treatment arm, using commercially available software (cvi42 version 4.1.3, Circle Cardiovascular Imaging Inc., Calgary, Canada and inTag version 1.0, CREATIS lab, Lyon, France) according to international standards for reporting of CMR studies [54].

LV volume and EF will be calculated from the short axis cine-stack using standard criteria to delineate cardiac borders [54]. Regional wall motion in 17 cardiac segments will be graded visually. Aortic cross sectional measurements will be made by manual planimetry of the endovascular-blood pool interface, at the times of maximal and minimal distension of the aorta. Aortic distensibility, compliance and stiffness index are calculated by standard methods using blood pressure measurements taken at the time of image acquisition with formulas and definitions listed in Table 2
[55].

**Table 2 Tab2:** **Definitions and formulas of parameters used in the assessment of arterial stiffness**

Parameter	Definition	Formula
Aortic Compliance	The absolute change in vessel diameter (or area) for a given change in pressure	ΔD/ΔP
Aortic Distensibility	The absolute change in vessel diameter (or area) for a given change in pressure	ΔD/(ΔP × D)
Stiffness Index	The ratio of the natural logarithm of SBP/DBP to the relative change in diameter	ln(Ps/Pd)/((Ds-Dd)/Dd)

Δ; change in; D, diameter; d, diastole; ln, natural logarithm; P, pressure; s, systole. Adapted from Oliver and Webb [55].

Native and post-contrast myocardial T1 will be measured [56]. Care will be taken to ensure a conservative region of interest and to avoid partial-volume effects from neighboring tissue or blood pool. Regions of interest are manually motion-corrected as required. The reciprocal of T1 is calculated as R1. ECV is calculated using the following equation [57]:
1

Where hct is the hematocrit. Myo pre and myo post are the pre-contrast and post-contrast myocardial T1 values. Blood pre and blood post are the pre-contrast and post-contrast blood pool T1 values. Strain analysis will use data from the tagged cine series. Endocardial and epicardial contours are drawn by a semi-automated process for each slice. Peak circumferential systolic strain and rotation will be calculated for the three short axis slices at the level of apex, mid-ventricle and base. LV twist is calculated by subtracting the basal rotation from the apical rotation. The method of determining torsion takes the radius and length of the heart into account, describing the torsion as the circumferential-longitudinal shear angle. This makes the measurement comparable between hearts of different sizes and is related to fiber orientation and processes in the myocardium [58, 59]. Basal and apical radius is calculated from measuring area by epicardial contours on cine imaging in diastole at the same slice location as the tagged images. Base-to-apex length is determined by subtracting the slice locations. The equation used to determine torsion is:
2

Myocardial perfusion will be assessed by visual comparison of stress and rest CMR perfusion scans (16 segments of the modified 16 segment American Heart Association/American College of Cardiology model) [60] with scores of 0 (normal), 1 (equivocal), 2 (non-transmural ischemia <50%), 3 (non-transmural ischemia ≥50%) or 4 (transmural ischemia). In addition, quantitative MBF estimates will be obtained using Fermi-constrained deconvolution, or other methods and myocardial perfusion reserve (MPR) calculated by dividing stress by rest MBF values [38].

LGE images will be analyzed visually by two experienced observers and any relevant patterns of enhancement are described based on a 17-segment model with scores of 0 (no hyperenhancement), 1 (1 to 25% mural thickness), 2 (26 to 50% mural thickness), 3 (51 to 75% mural thickness) or 4 (>75% mural thickness) allocated to each segment. Quantitative analysis of LGE will also be performed. LGE volume will be calculated across the whole LV stack by the modified Simpson’s method. To avoid confounding for artifacts, a conservative threshold for LGE is employed at five SDs from remote, normal myocardium. The amount of LGE will be presented as a percentage against normal myocardium.

